## 2. Methods

### 2.1. Objectives

The objective of this research is to evaluate the individualized clinical efficacy of TCM in the quantitative way (evidence-based GAS) by long-term observing the variation of symptoms and the corresponding adjustment of prescriptions after the individualized treatment of TCM on NSTE-ACS.

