### 2.2. Study Setting and Trial Design

This is observational research which will conduct at the Dongzhimen Hospital Affiliated to Beijing University of Chinese Medicine (BUCM), the Third Affiliated Hospital of BUCM, and the Beijing Hospital of Traditional Chinese Medicine Affiliated to Capital Medical University. This research has a prospective feature, which means that the admission period of patients will be between March 1, 2020, and August 31, 2020. We will include 200 hospitalized patients who were diagnosed as NSTE-ACS. Each included patient will be followed up by telephone or door visit every 2 weeks, collecting the individualized intervention of TCM and evaluating through the table of evidence-based GAS. The whole procedure of the research will consist of 6 times of follow-up. This protocol conforms to the statement of Strengthening the Reporting of Observational Studies in Epidemiology (STROBE) [11] (see Supplementary File 2) and is made some adjustments based on the adaptability for TCM.

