#### 2.6.5. Realistic Results

Professional evaluators will assign corresponding scores according to the completion of each goal at the arranged time point after the therapy. *T* score will be calculated by the difference between the score of baseline and result based on the completion of evidence-based GAS. It will be the final score of a patient to evaluate the characteristics of clinical therapy. Two factors should be taken into account when calculating the score: (1) different weight scores (*w*_*i*_) should be given due to the different degrees of each indicator; (2) the influence of quantity variance should be eliminated due to the number difference of each goal. The formula is listed as follows:(1)$$\begin{array}{c} \text{GAS}=50+\frac{10\sum^{}\left(W_{i}X_{i}\right)}{\sqrt{\left(\left(1-p\right)\sum^{}w_{i}^{2}+p\left(\sum^{}w_{i}^{2}\right)\right)}}. \end{array}$$

Note: *x*_*i*_ represents the score for the indicator of the item *i*; *w*_*i*_ represents the weight for the indicator of the item *i*; *p*=0.3.

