### 2.9. Statistical Analysis

The software SPSS version 19.0 will be used for statistical analysis. All statistical analysis will be in the significance level 0.05 and expressed by the 95% confidence interval (CI) or two-sided test. The description of quantitative indicators for baseline and the demographic feature will calculate the mean, standard deviation, median (distributed data), and maximum (distribution data). The description of qualitative indicators will calculate the frequency and percentage. Results of evidence-based GAS on different times will be analysed by the repeated measures ANOVA to observe the dynamic characteristics of individualized curative effect. Among the repeated measures ANOVA, the multivariable test (Pillai's trace, Wilks' lambda, Hotelling's trace, and Roy's largest root) will be used to judge the difference of efficiency at different time points; Mauchly's test of sphericity will be applied to determine whether the corrected test (Greenhouse–Geisser, Huynh–Feldt, and lower-bound) is needed; tests of within-subjects effects will be judged whether the result is consistent with the multivariable test; tests of within-subjects contrasts will evaluate whether the change of curative effect was in accordance with the form of the curve; tests of between-subjects effects will be used to determine whether the efficacy of pairwise comparison at each time point was statistically significant.

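### Section 2.6.5 leaves open whether T is a change or a level, and no test listed in 2.9 compares a follow-up with baseline, so the time tests do not by themselves answer the efficacy-by-self-control question

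*Protocol article*

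**What the plan says.** Section 2.1 states the aim: "The objective of this research is to evaluate the individualized clinical efficacy of TCM in the quantitative way". Section 2.4 says there is no control group and that patients serve as their own controls, so baseline is the only comparator. Section 2.2 sets the schedule: "Each included patient will be followed up by telephone or door visit every 2 weeks", and "The whole procedure of the research will consist of 6 times of follow-up".

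Section 2.6.5 describes the score in two ways. In words, scoring takes place after treatment ("Professional evaluators will assign corresponding scores according to the completion of each goal at the arranged time point after the therapy") and the T "score will be calculated by the difference between the score of baseline and result based on the completion of evidence-based GAS". The printed formula, however, takes the item scores *x* and weights *w*, adds 50, and contains no baseline term. Section 2.6.2 puts baseline at −1 in general (sometimes −2). Section 2.6.4 puts the expected, successful result at 0.

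Section 2.9 says: "Results of evidence-based GAS on different times will be analysed by the repeated measures ANOVA". It then assigns each block of output a job:
- The multivariate tests "will be used to judge the difference of efficiency at different time points".
- The within-subjects tests check agreement with the multivariate result.
- The contrasts describe the form of the curve.
- The between-subjects tests are assigned to pairwise comparison of time points.

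**The concern.** With self-control as the only comparator, the efficacy question is whether patients are better than at their own baseline. The tests in 2.9 ask whether time points differ from each other. The two questions coincide only if baseline is one of the time points.

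The text of 2.6.5 points the other way. If T is the difference between baseline and result, it exists only after baseline, once per follow-up. Equal means across visits then fit no benefit, a constant benefit and a constant worsening alike. A non-significant time test could accompany a prompt, lasting response, and a significant one could reflect a fading response. A reader who took that p-value as the efficacy result could be misled either way.

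**Working it through.** The plan gives no effect size, SD or power, so there is no planned figure to reproduce.

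**Step 1: what the printed formula gives.** As printed, the denominator is √[(1 − p)Σw² + pΣw²] = √Σw². With g goals of equal weight, all scored x, GAS = 50 + 10·g·x/√g = 50 + 10x√g.
- All goals at expectation (x = 0): 50.
- All goals at the usual baseline (x = −1): 50 − 10√3 = 32.7 for 3 goals, 50 − 10√4 = 30.0 for 4, and 50 − 10√5 = 27.6 for 5.

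On the formula, then, 50 means goals met as expected, and a baseline value can be computed. On the text, T is a change. Both cannot describe the same number.

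**Step 2: what the time tests see if T is a change score.** Write the mean at visit j as μⱼ = δ + τⱼ. Every time contrast is a difference of visit means, so δ cancels. The null τ₁ = … = τ₆ holds for δ = 0, δ = +10 and δ = −5 alike. This is algebra and does not depend on the SD or correlation.

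**Step 3: simulation.** From the documents: 200 patients, six visits, two-sided 0.05. Assumed: normal data, SD of the change score 5, 10 or 15, and equal correlation between visits of 0.3, 0.5 or 0.8. There were 1,000 runs per setting. With a single group the four multivariate statistics give the same F, so one Hotelling test represents them all.

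| Mean change over the six visits | Time test, follow-ups only | Baseline added as a level |
|---|---|---|
| 0 throughout | 4.4% to 5.9% | 4.1% to 5.7% |
| +5 or +10 throughout | 3.6% to 6.7% | 98.5% to 100% |
| −5 throughout | 4.4% to 6.0% | 98.5% to 100% |
| Waning 5 to 0 | 97.4% to 100% | 99.7% to 100% |
| Waning 10 to 0 | 100% | 100% |

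Adding baseline restores detection of a sustained shift. But +5 and −5 then reject about equally often, and waning still rejects, so the p-value carries neither direction nor timing.

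**Step 4: a direct comparison at one visit.** Take a mean change of 5 at a named follow-up, with the least favourable assumed SD of 15. The standard error is 15/√200 = 1.06, the ratio is 5/1.06 = 4.7, and power is about 99.7%. With SD 10 the ratio is 5/0.707 = 7.1 and power is essentially 100%.

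**Step 5: does the between-subjects output fill the gap?** With one group it contains only the intercept, which tests the grand mean against 0. On a 50-centred scale it rejected in 100% of runs, including those with no effect. It would be a test of average change only if T were a raw difference, and 2.9 assigns it to pairwise comparison instead.

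**The case against.** The strongest reply is that 2.9 does not list the levels of the time factor, the flow diagram is not available, and self-control is consistent with baseline being one of them. The printed formula yields a baseline T, and Table 2 has columns for baseline and results. On that reading a sustained response is detected. This stands, and it is why the loss of detection is conditional on the change-score reading.

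A second reply is that the analysis is meant to show the dynamics of the effect, that 2.1 also speaks of following symptom variation, and that rejecting under a waning response is correct for a test of difference. This also stands as a defence of the time tests for describing trajectory. It does not supply the comparison with baseline that efficacy by self-control requires.

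A third reply is that factor levels and contrasts are commonly left to an analysis plan. That would answer a complaint about missing detail. Here, however, 2.9 allocates the repeated-measures output test by test, and 2.6.5 contradicts itself on what is being tested.

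Two stronger readings are tempting. A reader might infer that no change means T = 50. The documents do not say so, and on the printed formula 50 is the expected result. A reader might also infer that the analysis will in general lose some 95 points of power. That figure belongs to an exactly flat profile. With SD 10 and equal correlation of 0.4 to 0.8, a linear drift of 3 points over the six visits gives the time test about 96% to 100% power, and a drift of 2 points about 63% to 99%. Those rejections, though, reflect the drift and not the level relative to baseline.

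**Conclusion.** The point holds in a conditional form. Without condition, the text and formula of 2.6.5 disagree on whether T is a change or a level, and no test listed in 2.9 compares a follow-up with baseline.

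Conditional on T being the change score the text describes, the time tests cannot separate sustained benefit, no effect and sustained worsening; each rejects at about the 5% level. That result is exact for a constant shift. The rejection rates for waning and for the direct comparisons rest on the assumed SDs, correlations and normality.

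If T is a level and baseline is a level of the time factor, a sustained shift would be found, but the direction and the visit at which efficacy is judged would remain unstated. The documents do not support the claim that the planned analysis must miss an early response. They support the claim that, as written, its p-value does not settle efficacy.

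**What to change.** First, settle in 2.6.5 whether T is an attained level or a change, and make the text and formula agree.

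Then state in 2.9 which time points form the levels of the time factor, and that efficacy is judged by the mean change from baseline at one prespecified follow-up (for example the last, at 6 × 2 = 12 weeks), with its 95% CI, tested against no change:
- If T is a level: follow-up T minus the same patient's baseline T, tested against 0. T should not be tested against 50, because patients who improved but fell short of expectation would then count as worse than no change.
- If T is a change score: T against its no-change value. This is 0 for a raw difference, and 50 only if differences are entered into the 50-centred formula.

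Keep the omnibus time test and the contrasts to describe the trajectory. The cost is a correction to 2.6.5, one or two sentences in 2.9, and one paired contrast or one-sample test in SPSS. No new data or patients are needed.

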### 2.10. Quality Control

All researchers will be received the train of protocol and method of evidence-based GAS. All physicians should conduct the protocol according to the standard operating procedure (SOP) in the future.

#### 2.10.1. Selection Bias

(1) Admission bias (Berkson's bias) [22]: the bias due to different admission rates of patients with different diseases in hospital-based researches. (2) Nonresponse bias [23]: the bias due to uncooperative of patients or unwilling to participate, lowering down the response rate. (3) Follow-up bias [24]: patients do not obey the observational plan during the follow-up period. (4) Assembly bias [24]: inconsistencies between factors of this research and factors besides this research that influence the outcome of the disease. (5) Exclusive bias: the false association between factors and disease resulted from the direct exclusion of some participants without strict selection according to the principle of equivalence. As for the method of control, the preventive measures such as restriction, matching, and randomization will be done to prevent confounding factors in the stage of study design; detailed data collection of potential confounding factors will be done in the stage of implantation; various measures of standardization or multivariate analysis will be done in the stage of analysis.

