#### 2.3.2. Inclusion and Exclusion Criteria

*Inclusion Criteria*. Participants who meet the following criteria will be included. (a) Male or female patients between 18 years old and 85 years old. (b) Conformed to the diagnosis of NSTE-ACS, including unstable angina and non-ST-segment elevation myocardial infarction (NSTEMI), and complied with the diagnosis of Xiong Bi. (c) Had clearly related symptoms of NSTE-ACS or Xiong Bi and the number of episodes of symptoms more than 2 times per week. (d) Time period of hospitalization between March 1, 2020, and August 31, 2020. (e) Agreed to sign the informed consent (see Supplementary File 1).
*Exclusion Criteria*. Participants who meet any of the following criteria will be excluded. (a) With a cardiogenic shock, heart rupture, or interventricular perforation. (b) Had the history of major organ surgery within one month along with active or tendency of bleeding. (c) Patients with implantable defibrillators or pacemakers. (d) With severe liver and kidney dysfunction, malignant tumor, or endocrine, urinary, blood system, nervous system, and other serious primary diseases. (e) With cardiovascular diseases including acute pericarditis, subacute infective endocarditis, aortic dissection, and/or severe arrhythmia. (f) With a history of serious allergies or allergic to Chinese or western medicine. (g) Female during the stage of pregnancy and breastfeeding stage. (h) Have participated in other clinical trials.

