### 2.4. Interventions

This protocol is the observational setting with no controlled group. The method of self-control is used to compare therapeutic efficiency. All included participants will not apply any particular interventions for the aim of scientific research. The tool of evidence-based GAS is the way of analysis and evaluation, which represents patients who can receive the individualized treatment of TCM or western medicine based on their situations. The only requirement is they should choose the TCM or combined therapy if they have a need to be treated by physicians.

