#### 2.10.3. Confounding Bias

This bias will be controlled by (1) preventing confounding factors with restriction and match; (2) collecting detailed and accurate data that may include confounding factors; and (3) taking various measures in the stage of analysis with the methods of standardization and multivariate analysis.

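### Matching and randomization are claimed against confounding in a single uncontrolled group, and change over time is read as TCM efficacy that the design cannot isolate

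*Protocol article*

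**What the plan says.** **Safeguards claimed.** Section 2.10.1 states that "the preventive measures such as restriction, matching, and randomization will be done to prevent confounding factors in the stage of study design". Section 2.10.3 lists "preventing confounding factors with restriction and match" as the first control for confounding. Both sections also promise collection of confounder data, and standardization or multivariate analysis at the analysis stage.

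**Design described.** Section 2.4 states: "This protocol is the observational setting with no controlled group". It adds: "The method of self-control is used to compare therapeutic efficiency". On allocation it says: "All included participants will not apply any particular interventions for the aim of scientific research". On treatment it refers to "patients who can receive the individualized treatment of TCM or western medicine based on their situations", and its next sentence requires TCM or combined therapy for those who need treatment.

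**Population.** Section 2.2 plans 200 hospitalized patients with NSTE-ACS, contacted every 2 weeks for 6 follow-ups. Section 2.3.2 requires "the number of episodes of symptoms more than 2 times per week".

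**Claim.** The objective in section 2.1 is "to evaluate the individualized clinical efficacy of TCM in the quantitative way". Section 2.9 analyses GAS scores over time by repeated measures ANOVA and calls what it observes a curative effect.

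**The concern.** There are two linked problems.

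First, the bias section promises protections that the design section rules out. A reader of sections 2.10.1 and 2.10.3 would believe that confounding was handled by allocation and by matched comparison.

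Second, the efficacy wording needs exactly such protections. The patients start in hospital with an acute syndrome and qualify by having frequent symptoms. Scores would be expected to improve for some of them whatever is given, and western treatment may run alongside TCM. By section 2.6.2 and Table 3, baseline is usually set at −1, and slight relief of chest pain scores 0. Section 2.6.4 counts level 0 as success, so a small improvement from any cause counts as success.

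At stake is the main conclusion. A significant time effect would be reported as TCM efficacy, apparently backed by safeguards that were never possible.

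**Working it through.** **1. Claimed safeguards against the design in section 2.4**

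| Safeguard | What it needs | What section 2.4 provides | Possible? |
|---|---|---|---|
| Randomization (2.10.1) | An allocation made by the study | No intervention applied for research | No |
| Matching (2.10.1, 2.10.3) | A comparator group | No control group; self-comparison | No |
| Restriction (2.10.1, 2.10.3) | Eligibility limits | Criteria in section 2.3.2 | Yes |

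These are design-stage statements, so no analysis plan could supply what is missing.

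**2. What the time test detects**

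The protocol has no power figure to reproduce. Section 2.5 sets 200 on feasibility and gives no effect size or SD.

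Inputs from the protocol: n = 200 (2.2); two-sided level 0.05 (2.9); 6 follow-ups (2.2), taken with baseline as 7 time points. Assumptions, not in the protocol: within-patient correlation ρ = 0.5, a linear non-TCM recovery, and a TCM effect of exactly zero.

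Detectable mean change, in SDs of the within-patient difference: (z₀.₉₇₅ + z_power)/√n.
- 80% power: (1.960 + 0.842)/14.14 = 0.198
- 90% power: (1.960 + 1.282)/14.14 = 0.229

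Chance of a significant before-after test when all of the change δ is non-TCM: Φ(δ√n − 1.96) + Φ(−δ√n − 1.96). For δ = 0.2 and n = 200, δ√n = 2.83, which gives Φ(0.87) ≈ 81%.

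The multivariate time test named in section 2.9 was simulated as Hotelling's T² with 2,000 runs per row. With one group, the four listed multivariate statistics give the same F.

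| Non-TCM recovery (SD) | Paired test, n = 200 | Paired test, n = 160 (20% loss assumed) | Simulated time test, n = 200 |
|---|---|---|---|
| 0 | 5% | 5% | 5% |
| 0.1 | 29% | 24% | 21% |
| 0.2 | 81% | 72% | 75% |
| 0.3 | 99% | 97% | 99% |
| 0.5 | 100% | 100% | 100% |

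The paired columns use SDs of the change and the simulation uses SDs of a single score. They share a scale because the SD of a difference is √(2(1 − ρ)), which is 1 at ρ = 0.5.

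Range for the correlation, paired test with a recovery of 0.2 SD of a single score:
- ρ = 0.3: δ = 0.2/√1.4 = 0.169; δ√n = 2.39; about 67%
- ρ = 0.7: δ = 0.2/√0.6 = 0.258; δ√n = 3.65; about 95%

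The zero row shows that the test is valid for the question whether scores changed. The other rows show that it answers that question whatever the cause.

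**The case against.** **The design is openly declared.** Section 2.4 says there is no control group, and the Discussion grades the evidence as low level. This stands: a single-group before-after study is a disclosed choice and is not the complaint. But the listed limitations mention recall and follow-up bias, and not natural recovery, regression to the mean or concurrent western treatment. The Discussion still credits the method with measuring the efficiency of TCM objectively.

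**The list in section 2.10.1 is only illustrative.** It is introduced as examples, but the sentence says that these measures will be carried out. Restriction is feasible and should stay.

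**Multivariate analysis is promised, and covariates may be listed elsewhere.** This also stands: the absence of a covariate list in an article is no defect. But adjustment within one group supplies no untreated course over time, so it cannot separate TCM from recovery or regression to the mean.

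**Stronger readings that the documents do not support.**
- A reader might infer that a significant result is certain. It is not: with recovery of 0.1 SD the time test is significant in about 21% of trials.
- A reader might infer that PCI would be credited to TCM. The protocol records PCI only as a MACE component (2.7.5), and in goal 5 of Table 3 a new event scores −2, which counts against treatment.
- A reader might infer a western-only group that could serve as a contrast. The sentence in section 2.4 that requires TCM or combined therapy does not intend one.
- A reader might infer that baseline is each patient's worst point. Section 2.6.2 calls it only the state before therapy.

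**Conclusion.** The point holds in two parts.

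The contradiction between sections 2.10.1 and 2.10.3 and section 2.4 rests on the text alone and needs no assumption: matching and randomization cannot be done in this study.

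The attribution problem follows from the design and population. Change over time in one group of acute inpatients, selected on symptom frequency and possibly on combined treatment, does not identify a TCM effect. Sections 2.1 and 2.9 word it as if it did.

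The percentages (about 21%, 75% and 99% for recovery of 0.1, 0.2 and 0.3 SD) illustrate how readily the test responds to non-TCM change. They rest on the assumed correlation of 0.5, a linear recovery and complete data on 200 patients. The protocol gives no figure for the actual amount of spontaneous recovery, so they do not predict this study's result.

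**What to change.** 1. In section 2.10.1, delete *matching, and randomization*; in section 2.10.3, delete *match*. Keep restriction and point to section 2.3.2.
2. Restate the objective in section 2.1, the *curative effect* wording in section 2.9 and the conclusions as change in goal attainment during usual care that includes TCM, without attribution to TCM.
3. Add natural recovery, regression to the mean and concurrent western treatment to the limitations in the Discussion.
4. Optionally, show trajectories by baseline treatment (TCM alone or combined) and by index diagnosis (unstable angina or NSTEMI), as exploratory description only. Do not adjust for PCI or post-baseline drug use. They belong to goals 5 and 3, so the score would be adjusted for its own components, and attribution would still not follow.

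Items 1 to 3 are text edits and need no new data. The cost is a weaker conclusion: the study can describe change under care that includes TCM, but cannot claim that TCM caused it. That claim would need a concurrent comparison group.
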